### Power calculation

An initial sample size will be considered, and iterative calculations will be performed until adequate statistical power is achieved. As a reference point, we will start from the figure of 304 participants reported in the literature for studies in the field of social sciences [49]. However, since our research area differs substantially and is focused on health sciences, this initial value will be adjusted accordingly based on the specific characteristics and requirements of the study.

## Discussion

This project is expected to generate impact at several levels: (1) undergraduate health students; (2) older adults; (3) teaching and research staff; and (4) a broader meso and macro level, including health and community institutions or services, as well as territorial or scientific dimensions.

At the student level, the intervention is expected to enhance knowledge in CGA (thorough assessment instruments), health promotion, and disease prevention, and apply theoretical knowledge learned in class to real-life situations. The administration of the Service-Learning evaluation questionnaire provides a comprehensive view of how students perceive their development across the formative, learning, and service dimensions, offering valuable insight into the added value of Service-Learning beyond traditional academic instruction.

Through the Service-Learning approach, students not only strengthen their technical competencies but also engage in meaningful interactions with older adults, fostering reflective practice, social awareness, and a sense of civic responsibility. This experiential component is a defining feature of Service-Learning and represents a crucial educational opportunity to integrate knowledge, skills, and attitudes in a real community context.

According to Dahlke et al. (2020) [50], meaningful learning experiences with older adults in various contexts are necessary to carefully plan how to disrupt negative perceptions that may arise during undergraduate training. Experiential education opportunities that allow university students to interact positively with older adults can help replace negative age-related beliefs [21]. Furthermore, improvements are expected in interpersonal and intrapersonal communication skills, critical thinking, problem-solving abilities, and interdisciplinary teamwork. The aim is to prepare the next generation of leaders in health-related fields, professionals capable of responding to the rapid and complex evolution of social and healthcare systems, in alignment with the integrated care model promoted by the Departments of Social Rights and Health of the Government of Catalonia.

For the older adult participants, the intervention will serve as a valuable source of feedback on their current health status. They will have the opportunity to learn healthy habits and lifestyles that support an improvement in their quality of life, contributing to active and healthy ageing. They also benefit from interaction with students, which stimulates their mental and emotional activity and may help reduce feelings of social isolation. Engaging in dialogue and sharing personal experiences can further strengthen their self-esteem and sense of belonging [51, 52].

Connecting undergraduate health students with older adults creates a highly positive impact on the community, as it promotes the formation of meaningful bonds that support mutual learning and intergenerational understanding. This approach clearly aligns with several Sustainable Development Goals (SDGs) of the 2030 Agenda, particularly SDG 3 (Good Health and Well-being), SDG 4 (Quality Education), and SDG 10 (Reduced Inequalities), promoting a more just, inclusive, and healthy society through citizen empowerment and the social responsibility of future healthcare professionals. Several studies agree that it is helpful both for the students who take part and for the people or communities who benefit from these projects [53]. Students often feel more confident and capable, and the chance to reflect on their experience helps them understand their own strengths and areas for improvement. It also allows them to connect what they learn in class with real-life situations [54]. In the United States, Service-Learning has also shown positive results in increasing students’ awareness of social issues and improving their attitudes towards older adults [55, 56] while simultaneously integrating course content with real-world experience [57]. In Europe, other studies have shown similar positive results in Service-Learning (SL) projects, where community engagement not only enhances academic outcomes and improves competences, such as “developing as health professionals”, but also fosters a sense of belonging and social responsibility contributing to students’ professional growth [58–62]. This project has the potential to facilitate early detection of frailty, promote healthy ageing, and strengthen connections between universities, primary care, and local resources.

From the perspective of the teaching staff involved, the project will foster the acquisition of new knowledge and the development of competencies such as interdisciplinary collaboration, specific skills in CGA, and the promotion of health and disease prevention. It will also support the development of effective teamwork and help define best practices in conducting comprehensive geriatric assessments.

At the meso and macro level university-wide, territorial, and scientific, the project will raise the visibility of the university facilities contributing to the university’s integration into the local territory. Partnerships with key health and social care institutions, will be strengthened. Results of the study will be disseminated through scientific publications, presentations at conferences on health and education, and communication via institutional and social media channels to reach both academic and community audiences. National and international dissemination activities will position the CGA workshop as a model that could be replicated by other institutions across Catalonia and beyond. This model could be adapted and transferred to other contexts with fewer resources or different demographic characteristics, such as rural areas or regions with limited access to geriatric care. Evaluating the model’s effectiveness in diverse settings would also be essential to guide adaptation. In addition, one of the potential benefits of this type of initiative is the reduction of healthcare system costs. By improving the training of future professionals and empowering older adults through more integrated and person-centered care, early detection and prevention strategies are reinforced, potentially decreasing the need for more complex or long-term interventions. This economic dimension supports the relevance and scalability of the model in both well-resourced and constrained settings. Overall, the project may contribute to preparing future professionals for the challenges of population ageing while positioning the university as an active agent in community well-being.

One of the strengths of this project is its innovative application of Service-Learning methodology to CGA and the measurement of intrinsic capacity involving undergraduate students interdisciplinary across different health-care fields. Moreover, it represents one of the few studies using the ICOPE tool worldwide. Notably, no previous initiatives using ICOPE have been reported in the Central Catalonia region. VIG-Frail has demonstrated both convergent and discriminant validity when compared with other instruments, such as the EuroQol-5D-5 L for quality of life and the Braden Scale for pressure injury risk. However, to date, no study has yet examined its correlation with ICOPE [63, 64]. A major strength of this study is the use of the validated questionnaire developed by León-Carrascosa et al. [65] which has not previously been applied to such a large and diverse sample of undergraduate health students. This will provide valuable evidence on the performance and generalisability of the instrument in the context of health-related education. Furthermore, no previous Service-Learning initiatives incorporating a CGA as a core component have been identified in the published literature, underscoring the innovative contribution of this project.

Compared to similar innovations, this project stands out for its strong integration between the community and the university environment. Previous studies have shown positive outcomes in Service-Learning projects, where community engagement not only enhances academic performance but also fosters a sense of belonging and social responsibility [58]. Also, this innovative association between ICOPE and NOC aims to open new avenues for integrated assessment models in geriatric care, potentially improving the interdisciplinary understanding of functional decline.

For the limitations, a risk management plan has been developed to address them. One anticipated challenge is participant recruitment, which may be mitigated through collaboration with key community organizations or by offering visits at user locations. Another potential limitation is the non-attendance of older adults on session days; this may be addressed by converting the session into a role-play, practical workshop, clinical case discussion, or report preparation. The absence of a control group may limit the evaluation of intervention effectiveness. On the other hand, the specific objectives of the assessment of students’ soft skills and older adults’ knowledge is based on self-perceived evaluations, which may limit the validity of the results. Additionally, no pre-post test will be administered, which could reduce the reliability of the findings. No imputation methods will be applied for missing data, only complete-case analysis will be performed, acknowledging that this approach may reduce the statistical power of the results. Lastly, logistical challenges may arise, such as managing space, scheduling, and ensuring multidisciplinary interaction among student groups.

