## Methods/design

### Aim, design and setting of the study

The study was registered in *Clinical Trials* with the registration number NCT06890325 on March 24, 2025 (https://clinicaltrials.gov/study/NCT06890325). It is a one-arm intervention study that employs a single-centre mixed-methods approach, following the experimental mixed-methods framework outlined by Creswell and Creswell (2018) [39]. The study aims to analyse undergraduate health students’ perceptions of their professional training through the Service-Learning methodology, focusing on three dimensions: formative, learning, and service. This community-based educational approach also contributes to enhancing health knowledge among participants aged 60 years and older.

The study will be carried out in the Osona region (Barcelona, Spain), at the University of Vic-Central University of Catalonia (UVic-UCC), in collaboration with various community centres including primary care centres, neighbourhood associations and social organisations within the local community, such as Equip d’Assitència Primària Vic - CAP El Remei Vic sud, ASHES – Associació per a la Sostenibilitat Humana, Ecològica i Social, the Associació de Veïns Horta Vermella, and the Germanetes dels Pobres de Vic.

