The next session will consist of a classroom-based student activity (without the older adults). During this session, students will prepare a report based on the CGA and will develop personalized health recommendations for the older adult, including health education strategies and suggestions for referral to appropriate community health assets and programs. The report will include: (1) a summary table of the common block results and key domains: frailty (VIG-Frail score), quality of life (EUROQOL-5D-5L), cognition, mobility, nutrition, vision, hearing, psychological status, social support, caregiver status, and urinary incontinence-interpreted based on the ICOPE and NOC responses; (2) a section on the (subject-depending) specific block, detailing the test used, its purpose, and results; and (3) a section with personalized health promotion and prevention recommendations, including community-based health resources aligned with the participant’s preferences and place of residence. All reports will be reviewed by the course professor and the project coordinator. This dual review process helps ensure the quality and consistency of the content before it is shared with the users.

The final session will include the visit from older adults. To improve adherence to the intervention plan, reminder phone calls will be made to participants before this session. During this visit, students will meet again at the university with the same older adults they assessed during the first visit and present the personalized health report prepared in class. The main objective of this session will be for students to explain their findings and recommendations, applying personalized recommendations to the specific case of the older adult. In cases where the participant is unable to attend the session in person, data collection will be conducted via telephone.

At the end of the intervention of each semester, focus groups with students, professors, and older adults will be conducted to explore their experiences and perceptions of the programme. Further details on the procedures and data collection methods for these focus groups are provided in the Data Collection Methods section.

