##### Older adults

A specific questionnaire was also developed for community dwelling older adults to evaluate their perceived knowledge of their own health status, their awareness of lifestyle habits and modifiable risk factors, their understanding of community health resources and assets, and their overall satisfaction with the experience. This questionnaire will be completed at the end of the final session. Detailed questions are available in the supplementary file.

All items for both target populations will be rated on a 5-point Likert scale (1 = “not at all” to 5 = “very much”). All questionnaires will be created and administered through the REDCap platform. Research team members have undergone prior training to ensure their standardized administration and the accuracy of data collection.

In addition to the self-reported questionnaire, several validated instruments will be used to assess the health status of the older adults. The instruments include ICOPE tool to assess intrinsic capacity [16], the validated VIG-Frail scale to evaluate frailty status [41], the EuroQol-5D-5L to measure quality of life and eighteen indicators of NOC. The EuroQol-5D-5L is a widely used instrument validated for measuring self-perceived health and quality of life and has normative reference values for the Spanish population [42, 43].

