At baseline, univariate associations between ICOPE, VIG-Frail, and the components of the NOC outcomes will be explored. To examine linear relationships between continuous variables, Pearson’s correlation coefficients will be calculated when normality assumptions are met; otherwise, Spearman’s rank correlation coefficients will be used. Statistical significance will be set at *p* < 0.05. When multiple comparisons are performed, Bonferroni correction will be applied to adjust the significance threshold accordingly. No imputation methods will be applied for missing data, only complete-case analysis will be performed. The quantitative data will be analysed using SPSS software (version 29.0).

Qualitative data from focus groups will be conducted online via Teams. Participants will sign an authorization for recording and image use. The analysis process will be conducted by using a modified version of Colaizzi’s 7-stage method, which draws upon Husserl’s descriptive phenomenological approach that aims to describe the essence of lived experiences from the first-person perspective. In-depth thematic analysis will be finalized [47]. Adherence to the Standards for Reporting Qualitative Research will be ensured throughout the study [48].

A Data Monitoring Committee (DMC) has been established, consisting of the Principal Investigator, the study coordinator, one expert in data analysis, and one expert in the data collection platform (REDCap). The DMC will conduct periodic reviews of the intervention to ensure its adherence and data quality and analysis. Also, will monitor study progress and would be responsible for any decision regarding early termination if unforeseen circumstances arise.

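### The complete-case-only rule is acknowledged to cost power, but for the older adults' single post-programme questionnaire it can also bias the estimates, and the first-visit data have no stated role in checking this

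*Protocol article*

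**What the plan says.** The Statistical analysis section fixes the rule for missing data: "No imputation methods will be applied for missing data, only complete-case analysis will be performed". The limitations paragraph of the Discussion repeats it, "acknowledging that this approach may reduce the statistical power of the results". Bias from non-response is not mentioned in either place.

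The outcome most exposed is the older adults' own questionnaire on knowledge, awareness of resources and satisfaction. Under Data collection methods, Older adults: "This questionnaire will be completed at the end of the final session". There is no earlier value of it: "Additionally, no pre-post test will be administered, which could reduce the reliability of the findings". There is no comparison group either: "It is a one-arm intervention study that employs a single-centre mixed-methods approach".

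The article expects some loss: "Another potential limitation is the non-attendance of older adults on session days". It also plans to limit it. Under Structure of the intervention, "reminder phone calls will be made to participants before this session", and "In cases where the participant is unable to attend the session in person, data collection will be conducted via telephone".

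At the first session the common block records sociodemographic data, ICOPE, VIG-Frail, EuroQol-5D-5L and NOC indicators. Their stated uses are the students' report, description of the sample and the baseline associations. No section uses them to compare people with and without the final questionnaire, or to adjust for missing answers.

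**The concern.** Loss of power and bias are different consequences of missing data. Dropping incomplete records always costs precision. It also shifts the estimate whenever those who answer would, on average, score differently from those who do not. Naming only the first tells the reader that a larger sample would solve the problem, which is untrue of the second.

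A link between health and non-response is plausible here. Both visits with older adults take place at the university, and participants must travel there alone or with a caregiver. These scores are the main quantitative evidence for the objective on the programme's impact on older adults' knowledge and satisfaction. With one arm and one measurement, nothing else in the quantitative data would show a distorted result. The word only in the missing-data rule also excludes weighting and imputation, although health measures that might predict non-response are collected at entry.

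**Working it through.** **Plan's own figure.** The article gives no non-response rate, no difference between responders and non-responders, and no standard deviation. The 304 under Power calculation is a provisional starting value borrowed from the literature, with no effect size, power or drop-out attached. It cannot be reproduced, and the point does not depend on it. Everything below is therefore illustrative, apart from the 10-15% frailty prevalence in people aged 65 and over (Background).

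**Step 1: bias of a complete-case mean.** With m the missing share,

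bias = m × (mean of responders − mean of non-responders).

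On the 1-5 scale:

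| Missing share | Gap 0 | Gap 0.25 | Gap 0.5 | Gap 1.0 |
|---|---|---|---|---|
| 5% | 0 | 0.013 | 0.025 | 0.05 |
| 10% | 0 | 0.025 | 0.05 | 0.10 |
| 20% | 0 | 0.05 | 0.10 | 0.20 |
| 30% | 0 | 0.075 | 0.15 | 0.30 |

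**Step 2: compare with the loss of precision.** Assume that all 304 are older adults and that the SD is 1. With 20% missing, 304 × 0.8 ≈ 243 remain. The standard error rises by 1/√0.8 = 1.118, and the 95% half-width goes from 1.96/√304 = 0.112 to 1.96/√243 = 0.126. A 0.5-point gap adds a bias of 0.10. That is nearly as large as the half-width, and more participants would not reduce it.

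**Step 3: share scoring 4 or more, two strata.** Let f be the frail share, pf and pn the shares scoring high among frail and non-frail, and cf and cn their completion rates (telephone included).

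- True share = f·pf + (1−f)·pn
- Complete-case share = [f·cf·pf + (1−f)·cn·pn] / [f·cf + (1−f)·cn]

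Assumed ranges: f 15-30%, pf 40-50%, pn 70%, cf 40-80%, cn 90-95%.

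- Smallest bias (f = 0.15, pf = 0.5, cf = 0.8, cn = 0.90): true 0.075 + 0.595 = 67.0%; complete-case (0.060 + 0.5355)/0.885 = 67.3%. Bias +0.3 points.
- Middle example (f = 0.30, pf = 0.4, cf = 0.6, cn = 0.90): true 0.12 + 0.49 = 61.0%; complete-case (0.072 + 0.441)/0.81 = 63.3%. Bias +2.3 points. The frail share falls from 30% to 0.18/0.81 = 22%.
- Largest bias (f = 0.30, pf = 0.4, cf = 0.4, cn = 0.95): true 61.0%; complete-case (0.048 + 0.4655)/0.785 = 65.4%. Bias +4.4 points.

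**Step 4: use the article's frailty figure.** Only f changes, to 10-15%.

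- Smallest (f = 0.10, pf = 0.5, cf = 0.8, cn = 0.90): true 68.0%; complete-case (0.040 + 0.567)/0.89 = 68.2%. Bias +0.2.
- Largest (f = 0.15, pf = 0.4, cf = 0.4, cn = 0.95): true 65.5%; complete-case (0.024 + 0.56525)/0.8675 = 67.9%. Bias +2.4.

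**Step 5: telephone follow-up that works.** With f = 0.15, pf = 0.4, cf = 0.90 and cn = 0.95: true 65.5%; complete-case (0.054 + 0.56525)/0.9425 = 65.7%. Bias +0.2 points. On the mean scale, with frail people scoring 0.5 lower, the same completion rates give a bias of 0.003. With equal completion it is zero.

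The sign is positive throughout because frail people were assumed both to score lower and to complete less often. That is an assumption, not a finding from the article.

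**The case against.** The strongest reply is that the problem may be very small. Reminder calls and telephone collection mean that someone who does not come back is not automatically missing; only those also not reached, or unwilling, are lost. The sample is selected to be fairly fit, since entry starts at 60, requires travel to the university and excludes cognitive impairment. The only frailty figure in the article is 10-15%, and completion of 40% among frail people has no source. With 10-15% frail and completion of 80% against 90%, the bias is 0.2 to 0.4 points. The 95% half-width for a share of 61% in 304 people is 1.96 × √(0.61 × 0.39/304) = 5.5 points. The article already concedes that it has no control group and no pre-test and relies on self-perceived measures, and it adds focus groups on the same questions. Finally, tables of completers against non-completers are often left to an analysis plan.

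Most of this stands as a limit on size and severity. Two things do not fall to it. The article does not leave missing data open: it states a rule that excludes any other method, and it states an incomplete consequence of that rule. The limitations it does concede are separate from selective non-response.

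A reader might infer more than this: that the results are biased towards fitter, more satisfied people, that first-visit data could put this right, and that those data go unused. The documents do not support that. They give no rate of loss and no difference between responders and non-responders. Satisfaction is measured only at the end, so baseline data cannot correct drop-out caused by dissatisfaction. The first-visit data are used for description and association; they merely have no stated role for missing data.

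**Conclusion.** The point holds as a modest one. For the older adults' post-programme questionnaire, complete-case analysis carries a risk of non-response bias as well as a loss of power, and the article acknowledges only the loss of power. Size and direction cannot be determined from the article. If frail people score lower and complete less often, the share scoring 4 or more is overstated by about 0.3 to 4.4 percentage points at 15-30% frail, and by 0.2 to 2.4 at the 10-15% cited in the Background. If telephone follow-up brings completion close to equal, or if responders and non-responders are alike, the bias is negligible. The change is worth making because it is cheap and uses data already collected, not because a distortion has been shown.

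**What to change.** In Statistical analysis, keep complete cases as the reference and add a planned sensitivity analysis for the older adults' questionnaire. Use inverse-probability-of-completion weighting or multiple imputation based on first-visit age, sex (the common block records gender), VIG-Frail, ICOPE and EuroQol-5D-5L. Compare completers and non-completers on the same variables.

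In the limitations paragraph of the Discussion, state the consequence of the complete-case rule as reduced power and possible non-response bias.

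The cost is slightly more analysis and no new data. The added analysis assumes that, given the baseline variables, non-response is unrelated to the answers that were not given. It will not correct drop-out driven by dissatisfaction, and the report should say so.
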